**Methods:**

The study design is a randomized clinical trial (NCT05945862), with intervention groups paired with control groups of the same grade. Four elementary schools were selected based on district socioeconomic status. The study will be carried out for 1 year in four phases: (1) initial measurements, including anthropometry, blood pressure, psychosocial diagnosis, family medical history, and behavior variables, such as nutrition knowledge, dietary intake, sleep time and quality, and physical activity; (2) intervention implementation based on social cognitive theory, the behavior change wheel with the capability, opportunity, and motivation influencing behavior theoretical framework, and the transtheoretical theory, covering topics related to nutrition and healthy eating, child health, personal and sleep hygiene, physical activity, psychosocial well-being, and motivation; (3) postintervention measurements, including initial and behavioral measurements and intervention indicators; and (4) 6-month postintervention evaluation using the same initial and behavioral measures as in phase 1. Baseline differences by age, sex, socioeconomic status, and location will be analyzed using chi-square tests (qualitative variables) and analysis of covariance (quantitative variables). Multiple linear regression will test potential baseline associations between dependent variables (anthropometrics and blood pressure) and independent variables (diet, exercise, sleep time, family interaction, psychosocial well-being, and perception of childhood obesity). For comparing changes between the intervention and control groups at postintervention and at 6-month postintervention in anthropometrics, blood pressure, and behavioral variables, we will use multilevel mixed-effects regression models, given the hierarchical structure of participants nested within schools and the repeated measurements over time. SPSS and STATA software will be used with a significance level of *P*<.05.

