### Study Design

The study design is a randomized controlled trial in which school groups (classrooms) will be randomized either to the intervention or control arm. Baseline measurements will be completed before group assignment, reducing the potential for selection bias. The randomization sequence will be generated using a computerized random number generator (IBM SPSS Statistics version 21.0) by a researcher not involved in the study. Classroom groups will be paired within each school and randomly assigned (1:1) to the intervention or control arm. Allocation will be revealed by the independent researcher only after baseline measurements are completed and the intervention curriculum has been designed. The study will be conducted over 1 year in 4 phases. In the initial diagnostic phase (phase 1), baseline obesity risk factors will be measured in both control and intervention arms, assessing family and sociodemographic variables (family interaction, diet quality at home, body image perception [BIP], and psychosocial well-being) and schoolchildren’s health variables (anthropometry, diet, and blood pressure). Parents in both arms will receive a report on their child’s diagnosis, and in the control group, some recommendations will be added to improve their health and eating habits. Phase 2 consists of implementing the curriculum during 4 months in the intervention arm. Phase 3, at the end of the intervention, consists of the evaluation of results from the intervention arm in terms of knowledge acquisition, effectiveness, retention, motivation to change, fidelity, and acceptability by schoolchildren; in both arms, changes in knowledge, anthropometrics, blood pressure, and behavior of schoolchildren in terms of diet quality, exercise practice, and sleep quality will be measured. Finally, in phase 4, after 6 months of the intervention, sustained changes in anthropometrics and behavior (same measurements as phase 1) will be measured. The study design is shown in Figure 1. The program will allow for ongoing contact with participants, thereby promoting their retention and measuring immediate and medium-term outcomes. Participants in the control group will receive a summary version of the intervention in the next school year.

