### Selection of Schools

The districts and neighborhoods with the lowest economic resources in the region were identified using socioeconomic census data from the National Institute of Statistics and Geography (INEGI, for its acronym in Spanish), and 4 elementary schools were selected according to logistical feasibility and resources: 1 in Loma de Bácum (representing the rural area) and 3 in Ciudad Obregón, Sonora, México (representing the urban area). An interview will be held with the school principals to present the proposal, and those who agree will be asked for written authorization. Within each school, an equal number of groups (classrooms paired by grade) will be selected for the intervention and control arms, allowing for approximate matching of participants by sex and age in each arm. This approach allows us to offer the program to at least half of the students in each school and to implement the intervention in as many schools as possible according to available resources.

The number of classrooms per school is determined by the existing school structure and logistical feasibility. Across the 4 schools, a total of 24 classrooms will be included (12 in the intervention arm and 12 in the control arm), with varying numbers of students (participants) per classroom, since student grouping is pre-established by the Ministry of Education at the beginning of the school year.

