### Statistical Analysis

The normal distribution of the data will be verified using skewness, kurtosis, and Kolmogorov-Smirnov tests. Quantitative data with nonnormal distribution will be mathematically transformed for parametric analysis, or alternatively, nonparametric analysis will be used. Means and SDs will be calculated for continuous variables and percentages for categorical variables. To test age, sex, socioeconomic status, and location baseline differences, we will use chi-square tests for qualitative demographic variables (eg, socioeconomic level, family medical history, sport practice, etc) and analysis of covariance for quantitative variables (eg, anthropometrics, dietary intakes, HEI, TMexD, sleep time, BIP, family interaction, and psychosocial well-being). To evaluate specific aim 1, potential baseline associations of dependent variables (eg, anthropometrics and blood pressure) with independent behavioral variables (eg, dietary intakes, exercise and sleep time, family interaction, psychosocial well-being, and perception of childhood obesity) will be tested using multiple linear regression, starting with univariate regression (*P*<.2 and biological plausibility). Models will be built by a combination of univariate analysis and forward stepwise model selection using *P*≤.05 and biological plausibility. Preliminary models will be assessed for possible interactions (*P*≤.1) between sex and other variables included in the model, for collinearity (variance inflation factor<10), and for linear regression assumptions (linearity, normality, and homoscedasticity) using residual plots. Specific aim 2 will use mixed methods (qualitative and quantitative) to analyze results in terms of retention, fidelity, and acceptability of the intervention by children and school administrators. Specific aim 3 will compare the changes between the experimental arms (intervention vs control) from baseline to postintervention and to the 6-month follow-up in anthropometrics, blood pressure, HEI, dietary intakes, PA, sleep time, and knowledge. Primary analyses will follow the intention-to-treat principle. Given the hierarchical structure of the data (students nested within classrooms and classrooms within schools) and the repeated measurements over time (baseline, postintervention, and 6-month follow-up), intervention effects will be evaluated using multilevel mixed-effects regression models. Due to the cluster-based allocation, the intraclass correlation will be considered, potential attrition will be monitored, and all analyses will account for clustering to provide valid inferences. Models will include fixed effects for study arm, time, and the arm×time interaction, and random effects for classroom and school to account for intracluster correlation. Baseline values of the outcomes and covariates will be included as appropriate. Effect estimates with 95% CIs will be reported. We will examine model assumptions and fit indices. SPSS (IBM SPSS Statistics version 21.0) and STATA (StataCorp version 14.0) software will be used, with a *P* value <.05 for all statistical analyses.

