
## Results

From October 2023 to August 2024, a total of 451 participants were recruited from 4 different elementary schools in Sonora, México. As of February 2026, the collected data are in the process of analysis and interpretation. Table 3 presents the current status of each stage of the protocol as of February 2026.

**Table 3. T3:** Current status of the research protocol.

	Participating schools			
	Nueva Creación (26EPR0373T^a^)	Miguel Hidalgo (26DPR1013P^a^)	Héroe de Nacozari (26DPR0251J^a^)	Gral. Plutarco Elías Calles (26DPR0250K^a^)
Training and program design	✓	✓	✓	✓
Selection of participating schools	✓	✓	✓	✓
Sample size, n	173	117	86	75
Initial measurements	✓	✓	✓	✓
Intervention	✓	✓	✓	✓
Final measurements	✓	✓	✓	✓
Follow-up (measurements at 6 months)	✓	✓	✓	✓
Date capture	✓	✓	✓	✓
Data analysis	✓	✓		
Data interpretation				

a Work Center Code of the primary school.

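### The random effects listed for Aim 3 do not give a cluster-valid standard error for arm×time: neither a child nor a classroom-by-time effect is listed, and the direction of the error depends on the outcome

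*Protocol article*

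**What the plan says.** Under Study Design, "school groups (classrooms) will be randomized either to the intervention or control arm", paired within each school and allocated 1:1. Selection of Schools gives 24 classrooms, 12 per arm, paired by grade. Results reports that "a total of 451 participants were recruited from 4 different elementary schools".

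Under Statistical Analysis, Aim 3 compares change between the arms. The data are described as students within classrooms within schools, with "repeated measurements over time (baseline, postintervention, and 6-month follow-up"). The fixed effects are arm, time and arm×time. The random effects are "random effects for classroom and school to account for intracluster correlation". The section also promises that "all analyses will account for clustering to provide valid inferences" and says that baseline values will be included where appropriate. The threshold is a *P* "value <.05 for all statistical analyses".

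The abstract justifies the multilevel model "given the hierarchical structure of participants nested within schools and the repeated measurements over time", without the classroom. The Discussion also still names repeated-measures ANOVA as a strength of the study.

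**The concern.** With baseline as one of the time levels, the intervention effect is the difference between arms in change. A random intercept for classroom or school describes differences that stay constant over time. Such differences subtract out of every change score, so they contribute nothing to the error of the arm×time contrast. What does contribute is classrooms changing by different amounts (teacher, peers, delivery of sessions), and no listed term carries that.

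The list also has no child effect, although each child is measured up to three times. Stable differences between children then fall into the residual, although they too cancel from change. The two omissions push the standard error in opposite directions.

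The same model serves every Aim 3 outcome: anthropometrics, blood pressure, diet, activity, sleep and knowledge. For some of these a real effect could be missed. For others, or once the missing child effect is put in alone, classroom drift could be reported as an intervention effect.

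**Working it through.** **Inputs from the article.** 24 classrooms, 12 per arm. 451 children (173 + 117 + 86 + 75 = 451, which agrees with the total given). Mean classroom size m = 451/24 = 18.8. Significance level .05, taken as two-sided. There is no power calculation or planned standard error to reproduce.

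**Assumptions (no values in the article).** ρ is the classroom ICC of change, 0 to 0.10. r is the within-child correlation between visits, 0.3 to 0.9. Classrooms are taken as equal in size.

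**Step 1. Cancellation.** Write the outcome of child i in classroom j at visit t as fixed part + u_j + c_ij + d_jt + e_ijt, where u_j is the classroom intercept, c_ij the child effect, d_jt classroom drift and e_ijt the residual. The change from baseline contains d_jt − d_j0 and e_ijt − e_ij0 but neither u_j nor c_ij. The school intercept drops out in the same way. The listed effects therefore leave the classroom part of the change unmodelled.

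**Step 2. Child effect added, classroom-by-time still absent.** The true variance of the contrast exceeds the model's by DEFF = 1 + (m − 1)ρ. The actual type I error is 2[1 − Φ(1.96/√DEFF)].

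**Step 3. Exactly the listed terms, no child effect.** The model takes the variance of a child's change as about 2σ², whereas it is about 2σ²(1 − r). The ratio of true to model variance is therefore about (1 − r) × DEFF.

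| ρ | DEFF | Step 2 | Step 3, r = 0.3 | Step 3, r = 0.5 |
|---|---|---|---|---|
| 0 | 1.00 | 5.0% | 2.5% | 0.6% |
| 0.01 | 1.18 | 7.1% | 2.8% | 1.2% |
| 0.02 | 1.36 | 9.2% | 4.8% | 2.0% |
| 0.05 | 1.89 | 15.4% | 10.2% | 4.8% |
| 0.10 | 2.78 | 24.0% | 16.8% | 10.8% |

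The Step 2 column is the formula. A null simulation (24 classrooms of 19 children, 3 visits, 4,000 runs per cell) agrees with it: 15.7% to 16.3% at ρ = 0.05 and 23.7% to 25.0% at ρ = 0.10. The Step 3 columns are from that simulation. At r = 0.7 the simulated Step 3 error runs from 0.0% to 4.4%, and at r = 0.9 it is 0.0% throughout.

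**Step 4. Where the listed model turns from conservative to anti-conservative.** This happens when (1 − r) × DEFF > 1, that is ρ > [1/(1 − r) − 1]/(m − 1). With m − 1 = 17.8:
- r = 0.3: 0.429/17.8 = 0.024
- r = 0.5: 1/17.8 = 0.056
- r = 0.7: 2.333/17.8 = 0.131
- r = 0.9: 9/17.8 = 0.51

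**Step 5. One worked setting.** Take a cross-sectional classroom ICC of 0.05 with 80% of it stable. The drift variance is 0.01 per visit, so 2 × 0.01 = 0.02 in the change. The child part of the change is 2 × 0.95 × (1 − r).
- r = 0.5: ρ = 0.02/0.97 = 0.021 and DEFF = 1.37. Type I error is 9.4% with a child effect. Without one the ratio is 0.5 × 1.37 = 0.68, giving 1.8%.
- r = 0.9: ρ = 0.02/0.21 = 0.095 and DEFF = 2.69. Type I error is 23.2% with a child effect. Without one the ratio is 0.27, giving nearly 0.

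**Step 6. After the repair.** With a classroom-by-time error term, the simulated type I error is 4.4% to 5.8% for a single contrast and 4.1% to 5.7% for the joint test, across the whole grid of ρ and r.

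**The case against.** The strongest defence is that the article never says intercept and never says that the list is complete. It states the full hierarchy, links it to the cluster allocation and commits to accounting for clustering. Covariance structure and degrees of freedom are often left to an analysis plan, which is not shown here. This stands in part: random intercepts are the ordinary reading, not a stated fact. But the article does more than stay silent. It names the random effects and says what they are for, and those terms do not do that job for arm×time.

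Second, a reader might infer that the effect will be tested as if children had been randomized, so that false positives rise. The document does not support that. Inflation for strongly tracking outcomes needs a child effect, which is not listed. With the listed terms alone, most of the cells examined lie at or below 5%, and error exceeds 5% only when tracking is low and classroom drift is large. Nor does the article state a method for degrees of freedom, so child-level degrees of freedom cannot be attributed to it.

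Third, the sentence on baseline values leaves room for follow-up values to be analysed with baseline as a covariate. A classroom intercept would not cancel from the arm effect in that analysis. This is fair, but the model as written has baseline as a repeated visit and arm×time as a term, so the valid route is not the one fixed.

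Fourth, the abstract may simply be shortening the hierarchy. That is likely. It calls for a wording correction and does not show that classrooms are left out of the analysis.

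**Conclusion.** The point holds as a wrong standard error, not as a general rise in false positives. On the ordinary reading, neither the model as listed nor the model with only a child effect added bases the arm×time standard error on the 24 randomized classrooms. With the listed terms alone, the test ranges from very conservative (near 0% at r = 0.9) to anti-conservative (16.8% at r = 0.3 and ρ = 0.10). With a child effect but no classroom-by-time term, type I error is about 7% to 24% for ρ from 0.01 to 0.10.

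The mechanism follows from the design and the listed terms. The size rests on assumed values of ρ and r, equal classroom sizes and all 24 classrooms contributing. If ρ were 0, adding the child effect alone would be enough (5.0%).

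**What to change.** State the Aim 3 random effects in full: child, and classroom-by-time with classroom as randomized, in addition to classroom and school. Fit by REML. Test arm×time with small-sample degrees of freedom (Satterthwaite or Kenward-Roger) based on classrooms and reflecting the within-school pairing. For a single change contrast on classroom means this is 24 − 2 = 22 if the pairing is ignored, and 12 − 1 = 11 if the 12 pairs are the unit. The diet and activity recalls are given only in grades 4 to 6, so those outcomes should use the classrooms that contribute.

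An alternative is to analyse follow-up values with baseline as a covariate and a classroom random effect. This can be done one visit at a time, or with a child effect if both visits are modelled together.

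Either way, report the comparison of classroom-mean changes as a check. Align the abstract with Statistical Analysis (students within classrooms within schools), and reconcile the Discussion's mention of repeated-measures ANOVA with the mixed model.

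The cost is a little more analysis work and, for some outcomes, wider confidence intervals. Table 3 marks data analysis as done for two of the four schools and interpretation for none, so the change can still be made before results are interpreted. It should be recorded as made after data collection.

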
## Results

From October 2023 to August 2024, a total of 451 participants were recruited from 4 different elementary schools in Sonora, México. As of February 2026, the collected data are in the process of analysis and interpretation. Table 3 presents the current status of each stage of the protocol as of February 2026.

**Table 3. T3:** Current status of the research protocol.

	Participating schools			
	Nueva Creación (26EPR0373T^a^)	Miguel Hidalgo (26DPR1013P^a^)	Héroe de Nacozari (26DPR0251J^a^)	Gral. Plutarco Elías Calles (26DPR0250K^a^)
Training and program design	✓	✓	✓	✓
Selection of participating schools	✓	✓	✓	✓
Sample size, n	173	117	86	75
Initial measurements	✓	✓	✓	✓
Intervention	✓	✓	✓	✓
Final measurements	✓	✓	✓	✓
Follow-up (measurements at 6 months)	✓	✓	✓	✓
Date capture	✓	✓	✓	✓
Data analysis	✓	✓		
Data interpretation				

a Work Center Code of the primary school.

## Discussion

Lifestyle interventions in early life are critical to reducing future disease risk and health care costs. During recent years, most of the research has been toward adult behavior [23], but recently, successful programs have been adapted to children and adolescents [21,33], representing an opportunity to extend their benefits to youth. For a greater probability of success, participant and setting characteristics should be accounted for. Places where children spend most of their time are school and home; schools represent a structured environment for the implementation of planned activities, fostering knowledge acquisition and sustainable behavioral changes. Within schools, a broader population is reached, and participants support each other, sharing experiences [25,26,74].

Two main biological models have been proposed to explain obesity: the carbohydrate-insulin model [64] and the energy balance model [75], the latter reinforced by current evidence on the high energy contribution of UPFs. Our intervention is primarily based on the carbohydrate-insulin framework, which posits that diets high in rapidly absorbed carbohydrates—often from UPFs, also high in energy, saturated fat, and sodium—promote hyperinsulinemia and adiposity. Accordingly, the intervention focused on improving carbohydrate quality and overall dietary patterns by reducing UPF consumption, along with structured PA to improve insulin sensitivity and body composition, and therefore reduce obesity. Secondary cardiometabolic outcomes were examined within this same framework, given the influence of diet and PA on metabolic and vascular health. Taken together, it is hypothesized that these behavioral changes improve insulin sensitivity, inflammation, and vascular function, thereby reducing cardiometabolic risk.

Theories such as the SCT, the TTT, and the BCW have been used as a framework in obesity studies. The SCT characterizes behavior, with self-efficacy as the greatest motivator and mediator of actions, highlighting the importance of setting goals, social and professional support [54]. Activities are planned from informing to putting practices into action to create a healthy lifestyle through education, motivation, persuasion, development of capacities, modeling, and training. The BCW indicates that for a change in behavior, capacity, opportunity, and motivation must be present [56]. With respect to the TTT, it assumes that behavior change develops in staggered stages, and while the intervention is implemented, participants may progress through stages as they increase awareness, motivation, and engagement in health-related behaviors [55]. In the present study, the transtheoretical model was used as part of the conceptual framework, and although participants were not formally classified into discrete stages, intervention activities were designed to target key processes across stages of change, progressing from awareness and outcome expectations (precontemplation/contemplation) to self-efficacy and planning (preparation), to practice (action), and finally to reinforcement and self-monitoring (action/maintenance).

Within the intervention, components align with constructs in Table 1, targeting cognitive, psychological, and physical capability through knowledge acquisition, skills training, and observational learning, while reflective and autonomous motivation were addressed by enhancing self-efficacy, outcome expectations, self-regulation, and reinforcement processes; social opportunity was incorporated through group-based activities, reducing contextual barriers to healthy behaviors. As summarized in Table 1, theoretical constructs from the SCT, COM-B, and transtheoretical model were operationalized using psychosocial and behavioral indicators assessed, in most cases, with validated instruments.

The study’s conceptual model in Figure 2 posits that the intervention influences outcomes indirectly through internal processes and individual factors. Mediating variables such as BIP and adherence to the TMexD, among others, strengthen personal and social resources, thereby facilitating the adoption and maintenance of healthy habits. Moderating variables (such as sex and location, etc) shape the context in which these changes occur and potentially influence how individuals interpret, assimilate, and respond to the intervention, ultimately modulating observed outcomes.

Regarding child nutrition, Bujtor et al [76] identified that unhealthy dietary patterns high in fat and sugary drinks were associated with impaired body composition and inflammatory biochemical parameters (ie, inflammatory cytokines, C-reactive protein, total cholesterol, triglycerides, glucose, and insulin) [77]. Likewise, healthy dietary patterns (ie, those rich in fruits and vegetables and low in UPF and sugary beverages) should be promoted from early childhood, given that children tend to exhibit greater food selectivity. With respect to PA patterns, studies reported that almost 50% of children and adolescents usually spend more time in sedentary activities (ie, screen time), consuming more sugary and salty foods, with an increase in weight and body fat [15,78]. On the contrary, an active PA pattern is associated with improvements in adiposity [79], self-esteem, mental health [80], quality of life, cognitive abilities, academic performance, etc [81]. Even low-intensity PA promotes favorable health changes in children and young people with obesity [1].

As reported by Heggmen and Zahl [82], children from rural communities have a higher risk of overweight, obesity, and unhealthy habits. Some causes include limited access to healthy foods, less space availability for PA, and less nutrition and health education. However, children from urban communities are also at risk of obesity due to their social environment: globalization, modernization, cultural changes, and low economic conditions [74]. This proposal includes participants from rural and urban communities and schoolchildren from mestizo and indigenous origins, ensuring equity, cultural relevance, and social justice, reducing the gap and improving external validity due to participants’ diversity [25-27].

Among the indicators of effectiveness are efficacy, acceptance, knowledge acquisition, motivation, etc [70-73]. Knowledge acquisition assesses participants’ learning process; by working on the learning constructs, a change in long-term habits could be achieved [24,78]. Other critical variables are motivation and willingness to change, adherence to the intervention, retention, and dropout rates, which will be assessed by directed questions and statistical techniques (ie, intention-to-treat analysis). Fidelity consists of evaluating the practices used to ensure that the intervention is reliably and validly applied and that changes after the sessions can be attributed to the intervention and not to external factors, reducing the likelihood of errors and bias. Regarding participants’ understanding and involvement, attention, positive attitude, active participation, class work, attendance lists, etc, will be assessed using checklists. Supervision instruments monitoring the organization, planning, execution, and use of the protocols and the curriculum manual are also important [83,84]. Acceptability indicates how participants perceive the intervention; if it is not well accepted, it can generate a lack of commitment and reduced effectiveness. Once participants take ownership of the intervention, they are more likely to maintain their practices even after the intervention ends [71,72].

Among the strengths are its reach and accessibility, as it was conducted in schools where children spend a lot of time, representing a realistic and ideal environment for a large number of participants, with a lower probability of withdrawal. School age represents a critical growth period in the formation of lasting habits, and children can be multiplying intervention agents in their families. Another strength is the involvement of rural and urban schools, which promotes equity and reduces the disparity in cardiometabolic risk between both communities. The experimental design using school groups as units optimizes resources and allows for a larger number of schools to be intervened. Another advantage is the comprehensive approach for assessing family habits such as adherence to the TMexD and psychosocial variables. Individual variables such as diet, sleep, and PA times are fundamental in lifestyle habits, and evaluating the intervention in terms of feasibility, viability, retention, and acceptability allows measurement of the sustainability of acquired skills over time. Regarding the use of repeated-measures ANOVA, this is a robust tool in this type of study evaluating participants at multiple times.

Among the limitations, classrooms were randomized within schools, which, while not the optimal design for this type of study, enabled us to offer the intervention to more participants in each school. Logistical and funding constraints limit a second-year waiting-list control design, leading us to prioritize implementation across multiple schools. School schedules (eg, recess, arrival, and dismissal) are structured to minimize interaction between classrooms, reducing the likelihood of contamination. Nevertheless, we acknowledge that some contamination may occur and will address this with appropriate statistical analyses. Another limitation is the relatively low sample size for this kind of study, since this type of design requires a larger number of participants and the use of robust statistical methods. However, our research design is comparable to similar studies [74].

The age of participants may also limit their responses, since younger schoolchildren find it difficult to express themselves and remember data (ie, quantity of food and time of PA). This could be improved through greater interaction between staff and participants to build trust and facilitate recall of daily activities, enhancing the accuracy of responses. Regarding the self-reported estimates of PA and dietary intake, they depend on short- and long-term memory, showing greater variability compared to other objective measures [85,86]. However, the 3-day physical activity recall and the 24h-R are validated instruments widely used in the child population [87,88]. The use of few repetitions of the 24h-R does not ensure the measurement of between- and within-person variability; however, administering more repetitions could increase the challenges inherent in data collection in children and adolescents, who may have difficulty sharing information about their behaviors and may experience mental burden and stress [89]. Another limitation is that other important social actors in the student’s life, such as parents, will not be involved; however, the involvement of teachers, and especially classmates, is possible. The curriculum implementation depends on the time available in the school curriculum itself; however, if the intervention begins alongside the school year, it optimizes time and makes it easier to complete it. Another opportunity for future studies is to include other crucial variables such as quality of life and self-esteem, which are important at this stage. Concerning multilevel models, these require larger sample sizes, involve more complex assumptions, and may be sensitive to model misspecification. However, these are well suited for group-randomized trials, as they account for data grouping, provide valid standard errors, accommodate missing or unbalanced data, and allow the simultaneous examination of individual- and group-level effects, thereby improving statistical efficiency and inference.

In conclusion, the proposed protocol represents a comprehensive program and an effective and feasible strategy to promote healthy lifestyles and prevent cardiometabolic diseases, addressing low-income schoolchildren in Mexico. It is important to continuously evaluate and adapt the intervention to ensure sustainability and expand its impact to other schools. The implementation of this program can significantly contribute to improving children’s health and well-being by fostering positive habits from an early age and reducing the risk of obesity and cardiometabolic complications.
